### 4.2 Inclusion criteria

Subjects aged over 1 year and less than 19 years will be eligible for inclusion if they have relapsing SSNS, defined as **having experienced 2 or more relapses in the preceding 12 months**. This will include the following groups:

- Subjects on no long-term immunosuppressive therapy;
- Subjects receiving long term maintenance prednisolone therapy at a dose of up to and including 15mg/m^2 on alternate days;
- Subjects receiving long term maintenance prednisolone therapy at a dose of up to and including 15mg/m^2 on alternate days in conjunction with other immunosuppressive therapies, including levamisole, ciclosporin, tacrolimus, MMF, mycophenolate sodium and azathioprine;
- Subjects receiving long-term immunosuppressive therapies, including levamisole, ciclosporin, tacrolimus, MMF, mycophenolate sodium and azathioprine without long term maintenance prednisolone therapy.
- Subjects who have previously received a course of oral or intravenous cyclophosphamide:
  - Must have experienced two relapses in the 12 months prior to randomisation (in keeping with all other subjects)
  - Must have experienced at least one of these relapses following completion of cyclophosphamide therapy
  - Must be at least 3 months post completion of oral or intravenous cyclophosphamide therapy.
- Subjects who have previously received a single dose or course of intravenous rituximab:

- Must have experienced two relapses in the 12 months prior to randomisation (in keeping with all other subjects)
- Must have experienced at least one of these relapses following completion of rituximab therapy
- Must be at least 3 months post completion of intravenous rituximab therapy.
- Parents and (where age appropriate) subject understand the definition of URTI and the need to commence study drug once this definition has been met.
- Written informed consent obtained from the subject's parents/guardians and written assent obtained from subject (where age appropriate). Subjects aged 16 years and above will provide their own written informed consent.

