#### **4.21 Study visits**

At the baseline visit:

- Confirmation of inclusion and exclusion criteria.
- Informed consent/assent.
- Randomisation and allocation of study number.

- Information will be captured on dates of last two relapses.
- Medical and drug history since diagnosis of nephrotic syndrome.
- A physical examination will be performed, including measurement of height, weight and blood pressure.
- Calculation of dose of study drug to be administered when URTI occurs and provision of written information for parents regarding this.
- Scoring of prednisolone adverse effects will be performed by use of a standardised proforma.
- In order to evaluate changes in subject behaviour associated with the different prednisolone regimens, the Achenbach Child Behaviour Checklist (ACBC) will be used. The ACBC is a standardised measure made up of 120 items measuring internalising (withdrawn, somatic complaints, anxiety/depression, thought problems) and externalising (social problems, attention problems, delinquent and aggressive) behaviour problems. A total Behavioural Problem score is calculated from these problem scales and forms the basis of comparison with age and gender-matched normative data.
- Information relating to quality of life will also be collected using the CHU-9D and EQ-5D (dependent upon subject age) and PedsQL questionnaires.

At subsequent study visits (months 3, 6, 9 and 12):

- Details will be collected about any URTI that has developed and whether study drug has been commenced.
- Information will be captured regarding recent history of relapse and any treatment received for this.
- Recent other medical/drug history will be recorded.
- Adverse events will be documented.
- A study drug compliance check will be performed (tablet count using counting triangle).
- A physical examination will be performed, including measurement of height, weight and blood pressure.
- Scoring of prednisolone adverse effects will be performed by use of a standardised proforma.
- Recalculation of dose of study drug to be administered when URTI occurs and provision of written information for parents regarding this.
- If 3 or more courses of study drug have been administered since previous visit, confirmation of parental understanding of definition of URTI.
- Information will be collected about consultations with health care professionals in primary care (including the home) and also in hospital (both outpatient and inpatient) and any treatment administered.

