## 21. APPENDIX 4: PREDNOS 2 QUESTIONNAIRES TABLE OF COMPLETION BY AGE

**PREDNOS 2 Questionnaires Table of Completion by Age**

| Age of Child (yrs) | Parent Completed Peds QL | Parent Completed Child Health Utility (CHU) 9D | Parent Completed Achenbach Childhood Behaviour Checklist | Parent completed EQ-5D |
|--------------------|--------------------------|------------------------------------------------|----------------------------------------------------------|------------------------|
| >1-1.5             | No form available        | No form available                              | No form available                                        | No form available      |
| 1.5-2              | No form available        | No form available                              | Use version 1.5-5 yrs                                    | No form available      |
| 2                  | Use version 2-4yrs       | No form available                              | Use version 1.5-5 yrs                                    | No form available      |
| 3                  | Use version 2-4yrs       | No form available                              | Use version 1.5-5 yrs                                    | No form available      |
| 4                  | Use version 2-4yrs       | No form available                              | Use version 1.5-5 yrs                                    | No form available      |
| 5                  | Use version 5-7yrs       | Use CHU-9D                                     | Use version 1.5-5 yrs                                    | No form available      |
| 6                  | Use version 5-7yrs       | Use CHU-9D                                     | Use version 6-18 yrs                                     | No form available      |
| 7                  | Use version 5-7yrs       | Use CHU-9D                                     | Use version 6-18 yrs                                     | No form available      |
| 8                  | Use version 8-12 yrs     | Use CHU-9D                                     | Use version 6-18 yrs                                     | No form available      |
| 9                  | Use version 8-12 yrs     | Use CHU-9D                                     | Use version 6-18 yrs                                     | No form available      |

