## **5.3. Analysis populations**

All primary analyses (primary and secondary outcomes including safety outcomes) will be based on the intention-to-treat (ITT) principle. Participants will be analysed in the intervention group to which they were randomised, and all participants shall be included whether or not they

received the allocated intervention following an URTI. This is to avoid any potential bias in the analysis.

The ITT population will not include all of the randomised population. Analyses will be based on a modified ITT population which will include only those participants who had an URTI over the 12 month follow up period. Excluding those participants who did not have an URTI will result in no bias as taking the study medication is conditional on them experiencing an URTI, and this should by chance be balanced between the two groups.

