### **9.6. Analysis methods – secondary outcomes**

The number of participants experiencing any relapse (i.e. both URTI-related and non URTI-related relapses), the number of participants having an escalation of background immunosuppressant therapy and the number of participants having a reduction of background immunosuppressant therapy will be presented and analysed as per the primary outcome measure.

The rate of URTI-related relapses and rate of any relapse will be presented in the first instance as numbers of participants who have a relapse with the respective percentage, and in the second instance as a median and IQR. An adjusted incidence rate ratio with 95% confidence interval will be estimated using a Poisson regression model. An offset for the length of time the participant was in the trial will be included in the model. Statistical significance of the treatment group parameter will be determined from the p-value generated by the model.

The cumulative dose of prednisolone received over the 12 month period will be presented as means with standard deviations and ranges. Adjusted mean differences along with 95% confidence intervals will be estimated using a linear regression model. Statistical significance of the treatment group parameter will be determined from the p-value generated by the model.

Adverse effect data will be tabulated at each time point (3, 6, 9 and 12 months) with statistical significance determined by a chi-squared or Fisher's exact test (as appropriate). We will also assess whether or not each adverse event occurred over the whole trial period by assessing all the 3, 6, 9 and 12 month data collectively.

Quality of life measures are taken at multiple time points, as is the Achenbach Behaviour Checklist Scores. Means and standard deviations will be summarised at each time point. Data will be analysed using mixed effect repeated measures models with the minimisation variable and the baseline questionnaire score included in the model as covariates. Time will be included as a continuous variable in the model. In the initial model, a treatment by time cross-term will be included in the model. If this is not significant, it will be considered that the treatment effect

is constant over time, and models without the treatment by time cross-term will be fitted. Adjusted mean differences between groups will be presented alongside the respective 95% confidence interval.

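### Children too young for a baseline PedsQL or Achenbach form drop out of a model that needs the baseline score, and the SAP does not say which Achenbach score is analysed across the form change at age 6

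*Combined protocol and SAP*

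**What the plan says.** **Age range.** Protocol 4.2: "Subjects aged over 1 year and less than 19 years will be eligible for inclusion".

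**Forms by age.** Appendix 4 enters "No form available" for the PedsQL in both bands below age 2, and for the Achenbach in the band from just over 1 to 1.5 years. From 1.5 years through age 5 the Achenbach entry is "Use version 1.5-5 yrs". From age 6 it is "Use version 6-18 yrs". Both questionnaires are scheduled at months 0, 3, 6, 9 and 12 (protocol 4.12).

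**Model.** SAP 9.6 specifies "mixed effect repeated measures models with the minimisation variable and the baseline questionnaire score included in the model as covariates". It adds: "Time will be included as a continuous variable in the model". There is no term for age or form version.

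**Missing data.** SAP 9.1 adjusts for baseline values where they exist and removes them only as a last step after non-convergence. SAP 9.3 analyses the data received and limits sensitivity analysis to the primary outcome. The SAP amendment table explains that the missing-data text for continuous secondary outcomes was deleted because repeated measures methods cope with missing data.

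**Scoring.** SAP 9.4 sets out PedsQL scoring item by item on a 0 to 100 scale for each of four age versions. It contains nothing on the Achenbach. Protocol 4.21 says "The ACBC is a standardised measure made up of 120 items", and bases comparison of its total problem score on norms matched for age and gender.

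**The concern.** A mixed model can use a child with some missing responses. It cannot use a row in which a covariate is missing, and the usual software omits such rows without comment. A child who enters before a form exists for that age has no baseline score at any visit, so all of that child's later scores are lost. The reason given for deleting the missing-data text therefore covers missed follow-up questionnaires but not this case.

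Behavioural effects of prednisolone are one of the open questions the trial was set up to answer (protocol 3.1), and quality of life is a named secondary outcome. The children lost would all be the youngest, and solely because of their age at entry.

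A second gap concerns the Achenbach alone. Children aged 5 at entry move to a different form during follow-up, and the SAP does not say which score is analysed or how the two forms are combined.

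**Working it through.** The plan states no figure for either questionnaire analysis. Its sample-size figures (250 before drop-out, 360 recruited) concern the primary outcome. They are used here only as denominators: 360 randomised, and about 360 × (1 − 0.24) = 274 in the modified ITT population, using the 24% without an URTI given in protocol 4.29.

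**1. Do these children supply follow-up scores?** A child entering at age *a* reaches age *A* at month 12 × (*A* − *a*). At nominal visit dates:

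- PedsQL (*A* = 2): entry at 1.75–2 gives 4 usable follow-up visits, 1.5–1.75 gives 3, 1.25–1.5 gives 2, and 1–1.25 gives 1. With entry ages even across the band, the mean is (4 + 3 + 2 + 1)/4 = 2.5 of 4.
- Achenbach (*A* = 1.5): entry at 1.25–1.5 gives 4 and 1–1.25 gives 3, a mean of 3.5 of 4.

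So nearly all produce at least one score. The two-week visit window could exclude a child who has only just turned 1.

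**2. How many children?** The documents give no age distribution, so three are assumed.

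| Assumed age at entry | Under 2: no baseline PedsQL | Under 1.5: no baseline Achenbach | Aged 5: form change due |
|---|---|---|---|
| Uniform 1–19 | 1/18 = 5.6% | 0.5/18 = 2.8% | 1/18 = 5.6% |
| Log-normal, median 6, log SD 0.5, truncated to 1–19 | 1.4% | 0.3% | 14.4% |
| Uniform 2–12 | 0% | 0% | 1/10 = 10% |

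The first row means 20 of 360 (15 of 274) for the PedsQL and 10 of 360 (8 of 274) for the Achenbach.

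**3. Precision lost.** If each dropped child carried full information, the standard error would rise by a factor √(1/(1 − share)). At the top of the range this is √(18/17) = 1.029 for the PedsQL and √(36/35) = 1.014 for the Achenbach. These are upper limits, because such children have fewer visits and no baseline.

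**4. Achenbach form change, only if raw scores were pooled.** Suppose a share *s* of children switch, at dates spread evenly over the year, and the forms differ by *d* SD. The expected artefact at month *t* is *s* × *d* × *t*/12, so the fitted slope over 12 months is *s* × *d*. A simulation agrees. It used 270 children, 1:1, four follow-up visits, within-child correlation about 0.6, baseline adjustment, no true treatment effect and 2,000 runs per setting.

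| Share switching | Apparent 12-month change, *d* = 0.5 | *d* = 1.0 | SE of treatment effect, *d* = 0 | *d* = 1.0 |
|---|---|---|---|---|
| 5.6% | 0.029 SD | 0.053 SD | 0.070 | 0.074 |
| 10% | 0.046 SD | 0.100 SD | 0.071 | 0.075 |
| 15% | 0.076 SD | 0.152 SD | 0.072 | 0.079 |

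With a form difference present, the mean treatment estimate stayed within 0.002 SD of zero. Rejection rates were 3.9% to 5.7% for the treatment effect and for treatment by time. The values of *d* are assumptions.

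**The case against.** **The SAP never orders row-wise deletion.** That is true: it is how software behaves, and SAP 9.1 speaks of baseline values where available. But that phrase reads as referring to outcomes that have a baseline measurement, and no rule says what to do with an individual child who lacks one. Followed as written, the model loses these children.

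**Few children are affected.** This stands. Eligibility needs steroid-sensitive disease with at least two relapses in the preceding 12 months, so a child barely over 1 would have to present, respond and relapse twice by then. The uniform 1–19 figures are probably too high, and the true share could be zero.

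**A reader might infer a breach of SAP 5.3**, which says "all participants shall be included whether or not they". The sentence continues to receipt of the allocated intervention after an URTI. It concerns treatment taken, not whether a questionnaire exists for a child's age, so it does not support that inference.

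**A reader might also infer that the form change will appear as change over time.** That requires raw scores to be pooled, and no passage says they are. Protocol 4.21 points to age- and gender-matched norms, and the SAP is to be read alongside the protocol. What remains is that SAP 9.4 does not name the score. Nor does every 5-year-old switch: the month-12 visit may fall two weeks early, so a child who has just turned 5 can finish on the younger form.

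**Conclusion.** The point holds as a minor one on secondary outcomes. Under standard fitting, SAP 9.6 discards follow-up PedsQL scores from children entering below 2 and Achenbach scores from those entering below 1.5. The share is 0% to 5.6% and 0% to 2.8% respectively under assumed age distributions, probably towards the low end. The cost is coverage of the youngest children and at most about 3% on the standard error. It is not bias in the arm contrast, because the exclusion depends only on age at entry and not on the arm.

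The Achenbach form change is a secondary matter of missing detail. If raw scores were pooled, visit means and the time slope would shift by about 0.03 to 0.15 SD under an assumed form difference of 0.5 to 1.0 SD, and the standard error would rise from about 0.071 to at most 0.079. The treatment difference, which is what SAP 9.6 reports, would remain unbiased. The PedsQL has no matching form-change problem of scale, since SAP 9.4 scores every version from 0 to 100.

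**What to change.** **SAP 9.6, both questionnaires.** Keep children without a baseline form in one of two ways:

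- fit the month-0 score as the first response, with a month-0 mean of its own held equal in the two arms, and apply the continuous-time and treatment-by-time terms to months 3 to 12; or
- fill the missing baseline with the overall mean and add a missing-baseline indicator.

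Either retains every child with a follow-up score. Report by arm how many had no form available at baseline.

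**SAP 9.4, Achenbach.** State that the outcome is the age- and sex-normed total problem score referred to in protocol 4.21. Add either a term for form version at each visit or a sensitivity analysis leaving out children who change form. Whether the norms fully align the two forms cannot be judged from these documents, which is the reason for that extra check.

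**Cost.** A few sentences of SAP text and a few lines of code, on data already being collected. The one drawback is reliance on published norms for the Achenbach.

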The secondary endpoints include both continuous and categorical data items. The dichotomous data (e.g. incidence of escalation of background immunosuppressive therapy) will be analysed as per the primary outcome. Continuous data (e.g. prednisolone dose, quality of life scores) will be expressed as means and standard deviations, with differences in means and 95% confidence intervals. Longitudinal plots of the data over time will be constructed for visual presentation of the data. Data will be analysed using mixed effect repeated measures models with the interventions specified as independent variables. Baseline data will be included in the model as a covariate.

Analyses will be of all randomised subjects using intention to treat, except for those who do not have an URTI following randomisation. Over the course of the study up to the 12th July 2016, the number of patients who have completed the trial without experiencing at least one URTI is approximately 24% which is higher than the originally estimated <10% at the start of the trial. Exclusion of these subjects will result in no bias as these drop-outs are not related to the treatment and should by chance be equally distributed across the two treatment arms (this will be monitored throughout the trial). Sensitivity analyses will be performed on the 12 month data analyses due to the issues raised above. These analyses will be fully outlined in the Statistical Analysis Plan, and will include analyses with subjects censored at point of treatment escalation.

The only subgroup analyses planned are by the background treatment regimen that the subjects are on at randomisation (no long-term treatment; on long term maintenance prednisolone therapy; on other immunosuppressant therapy with long term maintenance prednisolone therapy; on other immunosuppressant therapy without prednisolone); an analysis comparing those subjects on prednisolone versus those not on prednisolone; and an analysis comparing those subjects on other immunosuppressant therapy versus those not on other immunosuppressant therapy. The study is not powered to detect differences in treatment effect across these subgroups, so these analyses will be considered as hypothesis generating.

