# **5. Statistical Principles**

## **5.1. Confidence intervals and p-values**

All estimates of differences between groups will be presented with two-sided 95% confidence intervals, unless otherwise stated. P-values will be reported from two-sided tests at the 5% significance level.

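### SAP 9.6 lets an interaction pre-test, for which no power is justified, decide which Achenbach and PedsQL difference is reported

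*Combined protocol and SAP*

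**What the plan says.** SAP 9.6 covers the quality-of-life and behaviour questionnaires, which are taken at baseline and at 3, 6, 9 and 12 months. The model is a mixed repeated-measures model adjusted for background therapy and baseline score. Its time structure is set out in four steps:

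- Form of time: "Time will be included as a continuous variable in the model".
- First fit: "In the initial model, a treatment by time cross-term will be included in the model".
- Rule for removing that term: "If this is not significant, it will be considered that the treatment effect", after which the SAP concludes that the effect does not vary and refits without the term.
- Output: "Adjusted mean differences between groups will be presented alongside the respective 95% confidence interval".

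The section also says: "Means and standard deviations will be summarised at each time point". It names no covariance structure, no time point for the reported difference, and no output for the case where the cross-term is significant. It sets no separate level for the cross-term; SAP 5.1 gives the general rule: "P-values will be reported from two-sided tests at the 5% significance level". SAP 9.10 confines sensitivity analyses to the primary outcome.

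Protocol 4.29 describes the same family of model in outline, without a pre-test: "Data will be analysed using mixed effect repeated measures models with the interventions specified as independent variables". It adds longitudinal plots.

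**The concern.** A non-significant interaction does not show that an effect is constant; it may only show that the test could not see the change. Under this rule the p-value selects the model, so the quantity behind the reported difference is settled by the data rather than in advance. That would be so even if the pre-test were well powered.

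Three features add to this. A single continuous term, taken here as a straight line because no curve or visit factor is mentioned, is blind to a difference that appears mid-year and fades. The exposure is a six-day course at each URTI, which gives no reason to expect a straight-line drift between arms. And because no covariance structure is stated, the weight each visit carries in the constant-effect estimate is not fixed.

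What is at stake is the steroid-safety reading. Whether repeated short courses affect behaviour is one of the open questions the protocol lists. A difference present for part of the year could be reported as one constant figure, with an interval that does not describe any particular visit.

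**Working it through.** **Inputs.** From the documents: four post-baseline visits (Protocol 4.20); 1:1 allocation; 250 evaluable and 360 recruited (SAP 4.7), hence 125 per arm. The roughly 24% without an URTI in Protocol 4.29 would give 180 × 0.76 ≈ 137 per arm before other losses. Assumed, because the documents do not give them: SD 1 (effects in SD units) and correlation between visits, either compound symmetry (CS) or AR(1). Also assumed, because the SAP does not say: when the cross-term is kept, the fitted month-12 difference is the one reported.

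**The plan's own figure.** 50% against 32.5% at 80% power, two-sided 5%, gives 124 per arm, or 248 (stated 250). 250 / 0.70 = 357.1, or 358 (stated 360). It reproduces, but it concerns the binary primary outcome and says nothing about the interaction test.

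**Power of the pre-test.** Each visit's arm difference has variance 2/125 = 0.016. Squared deviations of 3, 6, 9, 12 from 7.5 sum to 45. Under CS the slope difference has SE = √(0.016(1 − ρ)/45). Example, ρ = 0.5 and a difference growing by 0.3 SD from month 3 to month 12: SE = 0.01333, slope 0.3/9 = 0.0333, z = 2.5, power 70.5%. Over the assumed range:

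| Growth, month 3 to 12 | CS 0.3 to 0.8 | AR(1) 0.5 to 0.8 |
|---|---|---|
| 0.2 SD | 29–75% | 22–36% |
| 0.3 SD | 56–98% | 43–67% |
| 0.4 SD | 80% to above 99% | 67–89% |

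For a non-monotone effect of 0, 0.4, 0.4, 0 SD (CS 0.5), the linear term has 5% power, against 97.5% for a 3-df test with categorical visits.

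**What is then reported, CS 0.6.** Slope SE = √(0.016 × 0.4/45) = 0.0119.

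- Effect of 0.3 SD at month 12 only: expected slope 4.5 × 0.3/45 = 0.03, z = 2.52, so the term is dropped with probability Φ(1.96 − 2.52) ≈ 29%.
- Effect of 0.3 SD at months 6 and 9 only: expected slope (−1.5 × 0.3 + 1.5 × 0.3)/45 = 0, so the term is dropped in 95% of trials. The constant-effect estimate then averages (0.3 + 0.3)/4 = 0.15, although the month-12 difference is 0.

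**Visit weights under an AR(1) 0.7 fit.** Weights are proportional to 1, 0.3, 0.3, 1. Dividing by 2.6 gives 0.385, 0.115, 0.115, 0.385. The months-6-and-9 effect then averages 2 × 0.115 × 0.3 = 0.07, against a true visit average of 0.15.

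**Coverage by simulation** (200,000 replicates, pre-test at |z| > 1.96):

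| Correlation | True difference at 3, 6, 9, 12 months | Month-12 coverage | Constant-effect mean (true visit average) |
|---|---|---|---|
| CS 0.6 | 0, 0, 0, 0.3 | 79% | 0.075 (0.075) |
| CS 0.6 | 0, 0.3, 0.3, 0 | 70% | 0.15 (0.15) |
| AR(1) 0.7 | 0, 0, 0, 0.3 | 78% | 0.385 × 0.3 = 0.115 (0.075) |
| AR(1) 0.7 | 0, 0.3, 0.3, 0 | 89% | 0.07 (0.15) |

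A truly linear effect from 0 to 0.3 SD gives month-12 coverage of 91% (CS 0.6) or 83% (AR(1) 0.7). Categorical visits give 95% throughout. With no treatment effect, type I error under the rule is 5.3–5.7% (CS).

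**The case against.** Much of the defence stands.

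- A reader might infer that the pre-test is underpowered. The documents do not establish this: they give no SD, correlation or target effect for these scales, and over the assumed range power runs from poor to excellent. All that can be said is that none is justified. The non-monotone case is a failure of shape, not of sample size.
- A reader might infer that the selection step makes the second-stage interval too narrow for what it estimates. With balanced visits the constant-effect and slope estimates are uncorrelated. Under CS 0.6 the interval covered the true visit average 95% of the time among trials that dropped the term, for every pattern tried.
- The 70–89% coverage is scored against a month-12 difference that the SAP never names as its target. Any average can miss a single visit.
- The 0.07 against 0.15 result needs an AR(1) fit. Equal visit weights, as a random-intercept model gives in balanced data, return 0.15 on the same data.
- The damaging patterns were chosen for illustration. Treatment is repeated at every URTI through the year, and with a constant effect month-12 coverage under the plan is about 94%.
- Visit means, SDs and plots would let a reader see a marked pattern.
- The protocol's silence on a pre-test is not a contradiction, because Protocol 4.29 calls itself a summary and defers to the SAP.

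None of this supplies the missing target. That coverage must be judged against an unnamed contrast is itself the gap, as is the unstated covariance. The visit summaries are unadjusted figures by arm, not adjusted differences with intervals.

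**Conclusion.** The point holds as a weakness in pre-specification for secondary outcomes. SAP 9.6 reads non-significance as constancy, so the Achenbach and PedsQL differences depend on a pre-test; it also leaves the significant branch, the contrast and the covariance undefined.

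The size is conditional. With 125 per arm, SD 1 and correlation 0.6 (CS) or 0.7 (AR(1)), the reported interval covers the month-12 difference in about 70–89% of trials when a 0.3 SD effect is confined to certain visits. Under CS the visit average is still covered at 95%, while under an AR(1) fit a months-6-and-9 effect averages 0.07 instead of 0.15. False positives hardly rise.

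It does not follow that the questionnaire analyses are invalid or that the trial's main conclusion is at risk. The primary analysis and sample size are unaffected. This is a worthwhile correction because it is cheap, not because the damage is large.

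**What to change.** In SAP 9.6:

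1. Delete the sentence that drops the cross-term when it is not significant.
2. Fit visit (3, 6, 9, 12 months) as categorical, with treatment by visit always retained, baseline score and background therapy as covariates, and an unstructured covariance.
3. Name the equally weighted average over the four visits as the headline contrast, reported whatever the interaction p-value.
4. Show the four adjusted visit-specific differences with 95% confidence intervals beside it.

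No new data are needed; the cost is wording and a few more model parameters. Precision barely changes. Under CS 0.6 the SE of the average is √(0.016 × (1 + 3 × 0.6)/4) = 0.106, the same as for the constant-effect model. Under AR(1) 0.7 it is √(0.016 × 10.846/16) = 0.104, where 10.846 is the sum of the correlation matrix, against √(0.016 × 1.7/2.6) = 0.102. A month-12 headline would cost more (√0.016 = 0.126), which is a reason to prefer the average.
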